## Name and description of all drugs used in the trial

### Treatment of subjects

The investigational medicinal product in this trial is liraglutide 3.0 mg. Liraglutide is a licensed drug. A placebo that is visually identical to liraglutide 3.0 mg will be used as a comparator. Novo Nordisk will supply Liraglutide 3.0 mg and placebo.

## 9.2 Concomitant medications

Concomitant medications will be recorded in the participant's medical records/CRF/eCRF and reviewed at each trial visit. For participants with T2D taking anti-diabetic medications, such as sulfonylureas, medication review will be throughout the trial period. Glucose monitoring will be commenced one week prior to randomisation and continued throughout the study period and the anti-diabetic medication will be adjusted accordingly. Careful monitoring of symptoms of hypoglycaemia will be carried out throughout the trial. The use of insulin, DPPIV-inhibitors, GLP-agonist or any medication known to cause weight gain or weight loss will not be permitted in this study. Also, people who are on these medications will not be recruited into the trial.

Liraglutide causes a delay in gastric emptying, and thereby has the potential to impact the absorption of concomitantly administered oral medications. Further details of interaction with other medicinal products and other forms of interaction with the IMP can be found in the SmPC.

## Investigational Medicinal Product

### Name and description of Investigational Medicinal Product

|               |                                                                                                                                |
|---------------|--------------------------------------------------------------------------------------------------------------------------------|
| Name:         | Liraglutide 3.0 mg                                                                                                             |
| Composition:  | Liraglutide, Disodium phosphate dehydrate, Propylene glycol, Phenol, Water for injection, Sodium hydroxide, Hydrochloric acid. |
| Manufacturer: | Novo Nordisk                                                                                                                   |

### Name and description of Non-Investigational Medicinal Product

|               |                                                                                                                   |
|---------------|-------------------------------------------------------------------------------------------------------------------|
| Name:         | Placebo                                                                                                           |
| Composition   | Disodium phosphate dehydrate, Propylene glycol, Phenol, Water for injection, Sodium hydroxide, Hydrochloric acid. |
| Manufacturer: | Novo Nordisk                                                                                                      |

## Dosages, modifications and method of administration

Dose escalation schedule of liraglutide 3.0 mg/ placebo is as following:

|                                | Dose
(pen-setting once daily
subcutaneously) | Weeks |
|--------------------------------|-------------------------------------------------------------|--------------|
| Dose escalation 4 weeks | 0.6 mg                                                      | 1            |
|                                | 1.2 mg                                                      | 2            |
|                                | 1.8 mg                                                      | 3            |
|                                | 2.4 mg                                                      | 4            |
| Maintenance dose        | 3.0 mg                                                      | 5 – 24       |

At the end of baseline visit, after randomisation, participants will be trained and instructed to inject liraglutide 3.0 mg /placebo once daily at any time of day, without regard to the timing of meals, but ideally establish a routine for the same time of each day. Liraglutide 3.0 mg/placebo can be injected subcutaneously in the abdomen, thigh, or upper arm. The injection site and timing can be changed without dose adjustment, but it is important to try and stick to similar timing each day. If a dose is missed, participants will be instructed to resume the once-daily regimen as prescribed with the next scheduled dose. An extra dose or increase in dose should not be taken to make up for the missed dose. If more than 3 days have elapsed since the last dose of liraglutide 3.0 mg or placebo patients will be instructed to reinstate liraglutide 3.0 mg or placebo at 0.6 mg daily pen setting and follow the dose escalation schedule till the scheduled end of the treatment period (i.e. the 24-week treatment period will not restart). Participants will be invited to attend pharmacy to collect liraglutide 3.0 mg/placebo pre-filled pens and the dispensing schedule will be as follow:

- Baseline visit: 5 pens (i.e. 1 box)
- Week 4 follow-up visit: 5 pens (i.e. 1 box)
- Week 8 follow-up visit: 13 pens (i.e. 2 boxes plus 3 pens)
- Week 17 follow-up visit: 5 pens (i.e. 1 box)

#### Drug accountability (liraglutide 3.0 mg/ placebo)

The drug aspects of the trial will be delegated by the CI to a delegated Lead Pharmacist. Novo Nordisk will supply liraglutide 3.0 mg and placebo. UCLH pharmacy will be responsible for storage and dispensing of liraglutide 3.0 mg and placebo according to handling and storage instructions as reported in the Summary Of Drug Arrangements (SODA).

A log of all received, used, partly used and unused trial products will be kept. The trial products will be dispensed to each participant as required according to treatment group. Proper storage conditions (outlined below) will be available and the temperature will be evaluated and recorded at least every working day. No trial product should be dispensed to any person not enrolled in the trial.

Not in use: The liraglutide 3.0 mg/placebo will be stored in a refrigerator at a temperature between +2°C and +8°C, protected from light and kept away from the freezer compartment. Under these conditions, the shelf life of liraglutide 3.0 mg/placebo pre-filled pens is of 30 months.

In use: After first opening the liraglutide 3.0 mg/placebo pre-filled pen can be stored for one month at temperatures below +30°C or in a refrigerator between +2°C and +8°C. The drug should never be kept at temperatures higher than 30°C; the cap should be kept on the pen to protect from light at all times.

498 All used/unused IMPs will be returned to site pharmacy, to be then updated in the drug  
499 accountability log in the pharmacy site file. Drug destruction will be conducted, once authorised by  
500 the sponsor and in accordance with local practice, or returned to Novo Nordisk and this will be  
501 documented in the drug destruction log in the hospital pharmacy file.

502 Detailed instructions are contained in the summary of drug arrangements.

### 503 Dose modifications

504 If participants are unable to tolerate an increased dose during dose escalation, delaying dose  
505 escalation for approximately one additional week will be considered. Liraglutide 3.0 mg/placebo will  
506 be discontinued, however, if a participant cannot tolerate the 3.0 mg dose, as efficacy has not been  
507 established at lower doses. Any dosage changes will be logged in a drug diary by participants and this  
508 will be reviewed at each trial visits.

### 509 Assessment of compliance

510 Compliance includes both adherences to IMP and Protocol study procedures. Subjects will be  
511 provided with a drug diary to record their home-dosing. Any missed dosage will be logged in the drug  
512 diary. This is a way to assess subject's compliance to the treatment. This will be reviewed at each trial  
513 visit. Percentage of IMP compliance acceptable for patient to continue on the trial is 80%. Non-  
514 compliance will be documented by the investigator in the medical notes and reported to the  
515 sponsor. Persistent non-compliance may lead to subject withdrawal from the study.

### 516 Recording and reporting of adverse events and reactions

517 Collection, recording and reporting of adverse events (including serious and non-serious events and  
518 reactions) to the sponsor will be completed according to the sponsor's SOP (INV/S05).

### 519 Definitions

| Term                                                                              | Definition                                                                                                                                                                                                                                                                                                                                                                                                                                                                                                          |
|-----------------------------------------------------------------------------------|---------------------------------------------------------------------------------------------------------------------------------------------------------------------------------------------------------------------------------------------------------------------------------------------------------------------------------------------------------------------------------------------------------------------------------------------------------------------------------------------------------------------|
| Adverse Event (AE)                                                                | Any untoward medical occurrence in a patient or clinical trial participant administered a medicinal product and which does not necessarily have a causal relationship with this treatment. Therefore an AE can be any unfavourable or unintended change in the structure (signs), function (symptoms) or chemistry (laboratory data) in a participant to whom an IMP or procedural intervention has been administered, including occurrences which are not necessarily caused by or related to that product. |
| Adverse Reaction (AR)                                                             | Any untoward and unintended response in a participant to an investigational medicinal product which is related to any dose administered to that participant.

This includes medication errors, uses outside of protocol (including misuse and abuse of product)                                                                                                                                                                                                                                 |
| Serious Adverse Event (SAE), Serious Adverse Reaction (SAR) or Unexpected Serious | Any adverse event, adverse reaction or unexpected adverse reaction, respectively, that: 

• results in death,

                                                                                                                                                                                                                                                                                                                                                         |

|                                                                                                                                                                                                                                                                                                                                                                                                                                     |                                                                                                                                                                                                                                                                                                                                                                                                                              |
|-------------------------------------------------------------------------------------------------------------------------------------------------------------------------------------------------------------------------------------------------------------------------------------------------------------------------------------------------------------------------------------------------------------------------------------|------------------------------------------------------------------------------------------------------------------------------------------------------------------------------------------------------------------------------------------------------------------------------------------------------------------------------------------------------------------------------------------------------------------------------|
| Adverse Reaction                                                                                                                                                                                                                                                                                                                                                                                                                    | 
 
• is life-threatening*,
 
• requires hospitalisation or prolongation of existing hospitalisation**,
 
• results in persistent or significant disability or incapacity, or
 
• consists of a congenital anomaly or birth defect
 
• Raises suspicion of transmission of infectious agents
 
                                                       |
| 
*A life- threatening event refers to an event in which the participant was at risk of death at the time of the event; it does not refer to an event which hypothetically might have caused death if it were more severe.
 
** Hospitalisation is defined as an in-patient admission, regardless of length of stay. Hospitalisation for pre-existing conditions, including elective procedures do not constitute an SAE.
 |                                                                                                                                                                                                                                                                                                                                                                                                                              |
| Unexpected adverse reaction                                                                                                                                                                                                                                                                                                                                                                                                         | 
An adverse reaction the nature and severity of which is not consistent with the information about the medicinal product in question set out:
 
(a) in the case of a product with a marketing authorization, in the summary of product characteristics for that product,
 
(b) in the case of any other investigational medicinal product, in the investigator's brochure relating to the trial in question.
 |
| Suspected Unexpected Serious Adverse Reaction (SUSAR)                                                                                                                                                                                                                                                                                                                                                                               | An unexpected adverse reaction which is also categorised as serious.                                                                                                                                                                                                                                                                                                                                                         |
| Important Medical Event                                                                                                                                                                                                                                                                                                                                                                                                             | These events may jeopardise the participant or may require an intervention to prevent one of the above characteristics/consequences. Such events should also be considered 'serious'.                                                                                                                                                                                                                                        |

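### The hospitalisation footnote in the SAE definition does not separate planned admission for an unchanged pre-existing condition from unplanned admission for on-treatment worsening

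*Combined protocol and SAP*

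**What the plan says.** The protocol's Definitions table makes an AE serious if it "requires hospitalisation or prolongation of existing hospitalisation". A footnote attached to that criterion has two sentences. The first sets the scope: "Hospitalisation is defined as an in-patient admission, regardless of length of stay". The second sets the exclusion: "Hospitalisation for pre-existing conditions, including elective procedures do not constitute an SAE".

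The same table defines an AE broadly: "an AE can be any unfavourable or unintended change in the structure (signs), function (symptoms) or chemistry (laboratory data". Death, life-threatening events, lasting disability and the remaining criteria stand separately and do not carry the hospitalisation footnote. The life-threatening criterion has its own footnote ("A life- threatening event refers to an event in which the participant was at risk of death at the time of the event"), which does not mention pre-existing conditions. A further row covers important medical events: "These events may jeopardise the participant or may require an intervention to prevent one of the above characteristics/consequences. Such events should also be considered 'serious".

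The Seriousness section refers back to this definition and adds no rule on worsening. Under Recording and reporting of adverse events and reactions, the whole process "will be completed according to the sponsor's SOP (INV/S05"), a document that is not part of the plan supplied.

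**The concern.** An exclusion of this kind normally serves to keep planned admissions for a stable condition out of the SAE count. Here the word for inclusion makes elective procedures one example of what is excluded, not the limit of the exclusion. With hospitalisation defined as any in-patient stay, emergency and planned admissions are treated alike.

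The situation is realistic in this trial. T2D status is a stratification factor, so participants with diabetes are expected. Section 9.2 foresees sulfonylurea users, provides for adjusting anti-diabetic drugs during the trial, and adds: "Careful monitoring of symptoms of hypoglycaemia will be carried out throughout the trial". The exclusion criteria remove only uncontrolled or unstable hypertension and eGFR below 30, so controlled hypertension and lesser renal impairment can be present at entry.

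At stake is whether an on-treatment deterioration that leads to admission enters the serious-event pathway. Two investigators reading the same table could classify the same admission differently.

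**Working it through.** No formula applies. The check is to set the rules side by side and follow an admission through them.

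1. **Is worsening an AE?** Yes. The AE definition covers any unfavourable change in signs, symptoms or laboratory values and makes no exception for a condition already present.
2. **Is an AE that needs admission serious?** Yes, under the hospitalisation criterion taken alone.
3. **Does the footnote withdraw that?** Read literally, yes, whenever the admission is for a pre-existing condition. No section of the protocol or SAP restores worsening or unplanned admissions.
4. **What follows from being non-serious?** The Expectedness table defines both of its categories only for events classed as serious, and the SUSAR definition requires seriousness. An event that loses its only serious criterion therefore gets neither assessment.

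Applied to four kinds of admission:

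| Admission | AE? | Hospitalisation criterion, footnote read literally | Other route to serious |
|---|---|---|---|
| Planned, pre-existing condition unchanged | No unfavourable change, so not as such | Excluded | None needed |
| Unplanned, pre-existing condition worse, no other criterion met | Yes | Excluded | Only the important-medical-event row, by judgement |
| Unplanned, pre-existing condition worse, and fatal, life-threatening or disabling | Yes | Excluded | Yes, through that other criterion |
| Unplanned, new condition | Yes | Met | Not needed |

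The problem lies in the second row. In the first row little is lost, because an unchanged condition is hardly an AE. In the third and fourth rows the event is still serious. In the second row the footnote removes a status that the AE definition and the hospitalisation criterion together would give, and only investigator judgement can restore it.

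5. **Size.** The documents give no admission rate, no expected number of participants with T2D and no split of admissions by cause, so no count can be derived. The only scale available is the planned arm size of 35, where one reclassified participant is 1/35 = 2.9% of an arm.

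**The case against.** The strongest reply is that the text can be read consistently. An SAE must first be an AE. On that reading the footnote covers admission for the existing condition itself, while on-treatment worsening is a new untoward change that requires admission. An emergency glycaemic admission after starting study drug would then count. This reading is available, but the footnote does not state it and a site could reasonably take the other one.

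Four further points limit the concern:

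- A reader might infer that all emergency admissions for worsening go uncounted as SAEs. The documents do not support that. The footnote hangs on one criterion, and the fatal, life-threatening, disabling and important-medical-event routes remain open.
- A reader might infer that most drug-related admissions could be labelled pre-existing. Nothing shows this. Personal history of pancreatitis, for example, is an exclusion criterion, so pancreatitis on trial would be a new event. Prior surgery and obesity do not make every later admission one for those conditions.
- A reader might infer a falsely favourable safety conclusion. That does not follow either. SAP section 5.4 summarises AEs by counts and describes no separate SAE summary, and clinical worsening is still recorded as an AE. This stands for symptoms. It is weaker for test results: under Recording adverse events, clinically significant abnormalities go to the medical notes and are said to reach the AE log and eCRF if assessed as serious. One classed as non-serious may therefore stay outside the counted data.
- The sponsor's SOP or the Data and Safety Monitoring Plan may contain a rule on worsening. Neither is available, so what sites would actually report cannot be settled. Nor do the documents say which routine safety data the DSMC sees.

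**Conclusion.** The point holds in a limited form. As written, the footnote does not distinguish planned admission for an unchanged condition from unplanned admission for worsening. It conflicts with the AE definition and sits uneasily with the important-medical-event row. The exposed events are those whose only ground for seriousness is the admission. Unless judged important medical events, they would not be SAEs, would receive no expectedness assessment and could not become SUSARs.

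This rests on a literal reading of the footnote and on no other document correcting it. The number of events affected cannot be estimated from the documents. The primary efficacy analysis is untouched.

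**What to change.** Replace the exclusion sentence in the footnote with a rule to this effect: *Planned or elective admission for a condition that was present before the baseline visit and has not worsened since does not meet the hospitalisation criterion. Unplanned admission for a pre-existing condition, or admission because such a condition has worsened, does meet it. The other criteria for seriousness, including important medical events, apply in every case.*

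A single stated reference point is needed because participants sign two consents, one for screening and one for the trial. The baseline visit is one choice. Another will serve if it is named. The sponsor should also check that SOP INV/S05 agrees with the revised footnote.

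The cost is one or two sentences in the protocol and a few more SAE forms. No treatment, visit or efficacy analysis changes.
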